## Abstract

**Background:**

Low back pain (LBP) is the leading cause of disability worldwide. Physical exercise, as a treatment, is beneficial for the improvement of quality of life in patients with LBP, and it is widely accepted.

**Objective:**

We aimed to develop a protocol for a feasibility study that is designed to compare the effectiveness of different interventions in reducing pain, functional, and psychosocial factors among patients with chronic LBP after 8 weeks of randomization.

**Methods:**

This is a study protocol for a randomized controlled trial that will consist of individuals with chronic LBP who are aged between 18 and 65 years. Participants will be allocated, through block randomization, to one of the following groups: the motor control exercises (MCEs), pain education, MCEs+pain education, and usual care groups. The primary outcome will be pain intensity, and the secondary outcomes will be the pressure pain threshold, which will be measured with a digital algometer; LBP-related disability; fears and beliefs; the fear of movement; quality of life; mood states; and levels of depression and anxiety. The trial was approved by the ethics committee for research involving human beings of the Federal University of Pelotas (reference number: 5.717.390) in September 2022, and it will be conducted until August 2023.

**Results:**

The researchers are being trained to apply the questionnaires and carry out the interventions. Patient recruitment will begin at the end of 2022 and results are expected to be achieved by August 2023.

**Conclusions:**

Our trial will provide preliminary data regarding the feasibility and safety of MCEs and pain education for patients with LBP. It will also provide preliminary outcome data that can be used to identify the most efficient intervention and the level of health care that should be implemented in public health services.

**Trial Registration:**

Brazilian Registry of Clinical Trials U1111-1221-4106; https://ensaiosclinicos.gov.br/rg/RBR-2xx2r2/

**International Registered Report Identifier (IRRID):**

PRR1-10.2196/31345

## Introduction

### Background

Low back pain (LBP) is the leading cause of disability worldwide [1], resulting in significant economic burden for individuals, families, communities, industries, and governments [2]. LBP is deemed a chronic condition when the duration of continuous pain in the sacral, lumbar, or lumbosacral region exceeds 3 months. This may or may not be accompanied by irradiation to the lower limbs, which is called *lumbosciatalgia* [3].

Despite the high prevalence of LBP, many individuals prefer to modify their tasks at work rather than seek help due to the fear of losing their job [4]. However, these modifications may worsen the pain, as they can trigger other symptoms. Studies have shown that biopsychosocial factors, such as catastrophization, kinesiophobia, anxiety, depression, stress, job dissatisfaction, and financial concerns, may be associated with LBP [5-7].

Chronic pain treatment through physical exercise is beneficial for the improvement of patients' quality of life, and it is widely accepted. Studies have demonstrated positive results with strength training, walking, and stretching practices, such as pain reduction and improvements in depression and sleep quality [8]. In addition, there is evidence indicating that a multidisciplinary, biopsychosocial rehabilitation approach is more effective than an isolated approach for the treatment and management of chronic LBP [9].

Among the recommended exercise practices, it has been noted that motor control exercises (MCEs) are widely used for the reduction of recurrent LBP [10]. These exercises involve the voluntary contraction of deep muscles, especially the transverse abdominis and multifidus muscles, and aim to promote the activation of trunk stabilizing muscles to reduce symptoms and improve mobility [11,12]. The prescription and development of these exercises should be gradual and individualized, respecting the pain threshold of each patient in order to reduce the functional disability and catastrophization of the individual [13].

Despite research advances in LBP treatment, further studies that compare the effects of different treatment approaches are warranted to gain better understanding and develop intervention strategies that may be applicable to individuals with chronic LBP. There is currently no consensus about the effectiveness of treatments that account for the pain, functionality, and psychological factors in these individuals. Furthermore, few studies present their intervention protocols in detail, making it difficult to apply their obtained results in clinical practice. Therefore, we aim to provide detailed intervention protocols for MCEs and health that are reproducible and serve as a reference for interested professionals.

### Goal of the Study

The primary aim of our study is to analyze the effectiveness of a program that includes MCEs and pain education. The secondary aims are (1) to clarify the effects of the program on pain outcomes, including the subjective intensity of pain and the pressure pain threshold, and compare the MCEs group (M-group) and MCEs+pain education group (MP-group) to the pain education group (P-group) and usual care group (U-group), the P-group and MP-group to the M-group and U-group, and all 4 groups; (2) to clarify the effects of MCEs on physiologic and psychologic stress measurements and compare the U-group to the M-group, the U-group and P-group to the M-group and MP-group, and all 4 groups; and (3) to clarify the effects of the pain education intervention on physiologic and psychologic stress measurements and compare the U-group to the P-group and U-group and the M-group to the P-group and MP-group.

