## Methods

### Study Design

Our study will be a parallel-group randomized controlled superiority trial with 4 arms, as shown in Figure 1. The target sample size is 900 individuals with LBP, who will be randomized (1:1:1:1 allocation) via computer-generated randomization. The groups will receive their assigned intervention according to the following allocations: (1) M-group, (2) P-group, and (3) MP-group; the U-group will receive the usual care intervention. Individuals will be instructed to not perform any form of physical exercise during the intervention period. We will compare the three types of interventions to determine their relative superiority to usual care.

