### Pain Education

The educational program will be based on the protocol described by Traeger et al [16] and will consist of a biopsychosocial approach to dealing with fears and clarifying behavioral beliefs about pain and movement. Additionally, the program will explain the influence of emotional symptoms (stress, anxiety, kinesiophobia, etc) on chronic pain; the influence of lack of sleep and physical activity on LBP, gradual exposure to physical activity, and daily movements; and the neurophysiology of pain. The program will include the following three major components: (1) clarifying any useless beliefs about the nature of LBP, (2) presenting key concepts of the biology of pain, and (3) evaluating patients’ understanding and discussing recovery. Participants who are randomized to the pain education intervention will participate in two 1-hour sessions of pain education that will be conducted by a physiotherapist. The physiotherapist will be appropriately trained for the study and will be contacted weekly for clarifications on doubts and possible further guidance. Multimedia Appendix 1 shows the 3 steps of the Pain Education Program.

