### MCEs and Pain Education

Individuals who are allocated to both interventions will receive guidance regarding the educational program for 1 hour during the first appointment, before participating in the MCE program for 8 weeks. The topics that will be covered throughout the treatment will be reinforced, emphasizing the factors for which individuals have more difficulty with changing their behavior.

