### Usual Care Intervention

Conventional intervention will be based on exercises that are usually performed in clinical practice. It will involve the active stretching of the posterior thigh muscles (hamstrings) by using a resistance band. The therapeutic exercises will include (1) isometric exercises that activate the muscles of the core region and stabilizers of the loin-pelvic region and hips (the transverse abdominis and multifidus muscles, oblique and rectus abdominal muscles, gluteus minimus, and gluteus maximus); (2) isotonic exercises for the lower limbs (hip abduction and adduction and hip flexion and extension); (3) exercises that focus on movement functionality, which will be augmented by breathing and body perception techniques, body realignment, and muscular and joint imbalance correction; (4) resistance exercises that involve using an elastic band to strengthen lower limb musculature; and (5) guidance for performing daily life activities and explaining the importance of staying active to prevent recurrence or increases in pain, which will be given spontaneously as an initiative of the responsible physiotherapist.

The exercise interventions will be conducted with groups of 3 patients, and the program will last for 8 weeks. Patients will receive care twice per week, totaling 16 visits. The patients cannot perform any other types of exercises during the study period. To maintain patients’ compliance with the program, researchers will contact them each week to inquire about the progress of the interventions.

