#### Random Allocation and Blinding

After the initial evaluation, the participants will be allocated, through block randomization, to receive different interventions, which will be conducted by physiotherapists. Individuals who fulfill the inclusion criteria will receive clarification about the objectives and the procedures that will performed in the research, and their consent will be requested by asking them to sign the informed consent form, of which the terms were approved by the ethics committees of the Federal University of Pelotas and the Health Department of Pelotas City.

The participants will then be referred to the physiotherapist who will be selecting the interventions according to the groups to which the participants will be allocated. The individuals who are allocated to the M-group, MP-group, and U-group will participate in 16 treatment sessions (2 sessions per week, totaling 8 weeks of treatment) with an average duration of 40 minutes.

It will not be possible to blind the physiotherapists who are responsible for the interventions due to the type of research that will be conducted. However, evaluators and patients will be blinded to the treatment groups. Nonblinding conditions will only occur in cases of health emergencies.

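### The comparisons named for the pain education aim (U versus P, and U+M versus P+MP) also carry the effect of usual-care exercise, so neither isolates education

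*Protocol article*

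**What the plan says.** Under Goal of the Study, aim (3) is "to clarify the effects of the pain education intervention on physiologic and psychologic stress measurements". The comparisons attached to it are "compare the U-group to the P-group and U-group and the M-group to the P-group and MP-group". Aim (2), for motor control exercise, first names U versus M, then U+P versus M+MP, then all four groups. On the same pattern, aim (3) names U versus P and then U+M versus P+MP. Aim (1), on pain, includes among its comparisons "the P-group and MP-group to the M-group and U-group", and also all four groups.

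The content of the arms is given elsewhere in the article:

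- **U:** an exercise programme that includes "isometric exercises that activate the muscles of the core region" (Usual Care Intervention).
- **Sessions:** "The individuals who are allocated to the M-group, MP-group, and U-group will participate in 16 treatment sessions" (Random Allocation and Blinding). P is not in that list.
- **P:** participants "will participate in two 1-hour sessions of pain education that will be conducted by a physiotherapist" (Pain Education).
- **MP:** participants "will receive guidance regarding the educational program for 1 hour during the first appointment" (MCEs and Pain Education), then follow the motor control programme for 8 weeks with the topics reinforced.
- **Other exercise:** "Individuals will be instructed to not perform any form of physical exercise during the intervention period" (Study Design).

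**The concern.** U+M versus P+MP is the education margin of a 2×2 factorial. It measures education only if U is the cell with neither component, so that U and P differ by education alone. Here, moving from U to P adds education and also takes away 16 exercise sessions. The article's Background section itself describes exercise as beneficial in chronic pain, so the part taken away should not be presumed inert.

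At stake is the answer to aim (3). If usual-care exercise works, a useful education programme can look weak, absent or harmful on the comparisons named for it. The comparison that holds the exercise programme constant, MP versus M, is not named for aim (3) on the most plausible reading.

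**Working it through.** **Inputs.** From Sample Size Calculation: SD 2.4, planned difference 1.5, 225 per group. From Study Design: equal allocation. From Statistical Analysis: α = 0.05, taken here as two-sided. The documents give no value for E or C. E = 0.75 and C from 0 to 1.5 (the planned difference) are assumptions. No dropout and no covariate adjustment are assumed.

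**The plan's own figure.** With n = 2(2.4/1.5)²(1.960 + z)², where z is the normal quantile for the power, a difference of 1.5 needs 41 per group at 80% power and 54 at 90%. The stated 225 is not reproduced. This point does not depend on it; 225 is used only to set standard errors.

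**Step 1, what each comparison estimates.** Measure benefit against no exercise and no education, and let effects add: M = X, P = E, MP = X + E, U = C.

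- P − U = E − C
- (P + MP)/2 − (M + U)/2 = ½(P − U) + ½(MP − M) = ½(E − C) + ½E = E − C/2
- MP − M = E

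X cancels from the pooled comparison; C does not. The split into ½(P − U) and ½(MP − M) is an identity and needs no additivity.

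**Step 2, standard errors.**

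- MP − M, or P − U: 2.4 × √(2/225) = 0.226
- Pooled: 2.4 × √(2/450) = 0.160

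**Step 3, illustration on the pain scale, E = 0.75.** The chance of a significant result in favour of education is Φ(expected difference/SE − 1.960).

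| C | P − U expects | Pooled expects | Pooled, chance favouring education | MP − M expects |
|---|---|---|---|---|
| 0 | 0.75 | 0.75 | 99.7% | 0.75 |
| 0.5 | 0.25 | 0.50 | 87.8% | 0.75 |
| 1.0 | −0.25 | 0.25 | 34.6% | 0.75 |
| 1.5 | −0.75 | 0 | 2.5% | 0.75 |

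**Step 4, power of MP versus M at 0.75 points.**

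- Unadjusted: 0.75/0.226 = 3.31, and Φ(3.31 − 1.96) = 91%.
- Bonferroni over six pairs, α = 0.05/6, critical value 2.638: Φ(3.31 − 2.64) = 75%.

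The difference detectable with 90% power is (1.960 + 1.282) × 0.226 = 0.73 unadjusted and (2.638 + 1.282) × 0.226 = 0.89 with Bonferroni. Both are below the planned 1.5.

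**The case against.** **The sentence can be divided differently.** It could mean U against P and U, and M against P and MP. MP versus M would then be named, at least within a set. But that division compares U with itself, and it still keeps U versus P. The reading used here rests on the parallel with aim (2). It is the more plausible one, not a certainty.

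**Aim (1) is not an education aim.** This stands. A reader might infer that aim (1) makes the same mistake for pain. It concerns the effects of the programme, does not call P+MP versus M+U an education effect, and also names all four groups. Only a caution carries over, for anyone who reads that comparison as education.

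**The figures are on the wrong outcome.** This also stands. Aim (3) concerns stress measures, and the SD of 2.4 belongs to pain. The starkest rows need C larger than E. The table shows the direction and weight of the distortion, not the harm to aim (3).

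**MP versus M is available anyway.** Very probably: Statistical Analysis plans a four-group model with Bonferroni post hoc tests, and specifies no pooled comparison. A reader might infer that the trial cannot answer the education question; the documents do not support that. But the analysis section does not tie MP versus M to aim (3), and by this route its power at 0.75 points is about 75%, not 91%.

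**U versus P is a legitimate question.** Agreed. A finding that P is worse than U would correctly say that education alone is inferior to usual-care exercise. It would not show that education does nothing. It would be wrong to infer from this point that U is a bad comparator.

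**The arms are less distinct than described, and MP is not P plus exercise.** P is encouraged to stay active, and U may include informal advice on activity. Such advice further blurs U as a no-education control. MP receives 1 hour of education plus reinforcement and P receives two, so MP versus M estimates education as given in MP.

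**Conclusion.** The concern holds as a minor one. On the most plausible reading of aim (3), both named comparisons mix education with the loss of usual-care exercise: at full weight in U versus P (E − C) and at half weight in the pooled comparison (E − C/2). Neither equals E unless C = 0. This rests on additive effects and on the reading by analogy with aim (2). The sizes shown also rest on assumed E and C and on the pain SD. The comparisons of each intervention with usual care that Study Design sets out are unaffected.

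**What to change.** In Goal of the Study, reword aim (3) along these lines: the effect of adding pain education (1 hour plus reinforcement) to motor control exercise is estimated by MP versus M; P versus U is reported as pain education alone compared with the usual-care exercise programme. Do not interpret U+M versus P+MP as the education effect, and apply the same caution to P+MP versus M+U in aim (1) if it is ever read that way. Leave the U-group as it is.

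The cost is wording and some precision. Arms, visits and sample size do not change. MP versus M uses 225 against 225 instead of 450 against 450, so the standard error is 0.226 instead of 0.160. The comparison does not answer what the two-hour version of education would do on top of exercise.

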## Methods

### Study Design

Our study will be a parallel-group randomized controlled superiority trial with 4 arms, as shown in Figure 1. The target sample size is 900 individuals with LBP, who will be randomized (1:1:1:1 allocation) via computer-generated randomization. The groups will receive their assigned intervention according to the following allocations: (1) M-group, (2) P-group, and (3) MP-group; the U-group will receive the usual care intervention. Individuals will be instructed to not perform any form of physical exercise during the intervention period. We will compare the three types of interventions to determine their relative superiority to usual care.

**Figure 1 figure1:**
[figure not shown]
Flowchart of the study design.

### Ethics Approval

The study protocol was registered in the Brazilian Registry of Clinical Trials (registration code: RBR-2xx2r2; universal trial number: U1111-1221-4106). This protocol was created according to the SPIRIT (Standard Protocol Items: Recommendations for Randomized Trials) 2013 guidelines checklist [14].

Our research was approved by the ethics committee for research involving human beings of the Federal University of Pelotas (reference number: 5.717.390) in September 2022, and it will be conducted until August 2023.

### Recruitment

We will recruit individuals with LBP at outpatient clinics of basic health units in Pelotas, Brazil, while they wait for an evaluation. During recruitment, we will determine their study eligibility based on the inclusion and exclusion criteria in Textbox 1.

Individuals will be randomly allocated to intervention groups, having the same probability of being allocated to a group that will be exposed to the test interventions or the control group.

Inclusion and exclusion criteria.
**Inclusion criteria**
History of low back pain in the last 6 monthsPain intensity of ≥3 (Numeric Pain Rating Scale) during movement in at least one direction (flexion, extension, or rotation)Aged between 18 and 65 years
**Exclusion criteria**
Previous history of rheumatic disease, lumbar myelopathy, tumors, or central or peripheral neurological disordersHistory of major trauma, fractures, or surgery in the lumbar region or signs of nerve root compression (major muscle weakness affecting the lower limbs, reduction or abolition of patellar and calcaneal reflexes, and decreased sensitivity in lower limb dermatomes)

### Intervention Program

The physiotherapists who will participate in the clinical trial will undergo prior training to standardize the interventions.

The interventions will be divided into the following groups:

Group 1 (MCEs): individuals will perform a strengthening and stabilization exercise program for core muscles (stabilizers of the lumbar, pelvic, and abdominal muscles and the diaphragm muscle) and postural correction.Group 2 (pain education): individuals will receive a postural care guide and will be encouraged to remain active, performing their daily living activities within their limitations.Group 3 (MCEs+pain education): individuals will receive intervention through physical exercises and pain education.Group 4 (usual care intervention): individuals will undergo the usual treatment through the use of resources and the application of conventional techniques.

### The MCE Program

The purpose of the MCE program is to normalize the difficulty in the motion domain for each participant. The exercises will be divided into 3 stages of training. A progressive increase in the level of difficulty will occur as the patients correctly perform the exercises with ideal movement patterns (Table 1). A detailed anamnesis and physical examination will be performed to account for the condition of each individual participant. Additionally, these will allow us to determine the levels and goals for each stage of exercise and the progression time for each difficulty level.

In the first stage, individuals will start to learn how to perform isometric contractions of the transverse abdominis and multifidus muscles in the prone, supine, and quadrupedal positions. To ensure the correct activation of the transverse abdominis, it will be emphasized to participants that the lower part of the anterior abdominal wall (ie, below the level of the umbilical scar) should be pushed toward the spine to activate the muscle. Participants will be instructed to progressively increase the waiting time and number of contractions to up to 10 contraction repetitions×10 seconds of sustainment. At the first appointment, patients will receive awareness-raising advice for performing the deep muscle contractions and instructions on how to activate the aforementioned muscles, so that they can sustain the contractions during the exercises for about 30 to 45 minutes throughout the appointments. The patients will advance to the next stage when they show the ability to perform the exercise and control pelvic and lumbar movements with minimal effort while moving their upper and lower extremities.

In the second stage, the complexity of the exercises will be increased by progressing to functional exercises that involve performing trunk and upper limb coordination while maintaining trunk stability [15]. Patients will be taught to perform abdominal cocontraction in different postures and control movements of the lumbopelvic region with minimal effort while performing functional activities.

After learning all of the exercises in stages 1 and 2, participants will be instructed to perform trunk coordination exercises and weight loading for the upper limbs (ie, while maintaining the stability of the trunk) and consider the activities that presented difficulty or the activities for which they reported pain during implementation in the initial evaluation.

The last 10 minutes of appointments will be reserved for returning to baseline through free walking and stretching exercises.

**Table 1 table1:** Progression of the exercises in the different stages of the motor control exercises.

	Phase 1	Phase 2	Phase 3
Progression 1	Prone position (10 repetitions×10 seconds of sustainment)	Supine position with alternating hip flexion Bridge exercise (isometric hip lift; 10 repetitions×20 seconds of sustainment)	Gym ball and dumbbell lifting in supine positiona
Progression 2	Supine position (10 repetitions×10 seconds of sustainment)	Quadrupedal position with alternating shoulder flexion and hip extension	Gym ball or dumbbell lifting in sitting and standing positionsa
Progression 3	Quadrupedal position (10 repetitions×10 seconds of sustainment)	Squats (20 repetitions) Elevation of upper limbs in sitting and standing positions (20 repetitions)	Hold weight in hands while simultaneously performing activities (sitting, standing, walking, and climbing stairs)^a^

^a^Progression will be determined according to the patient's functional condition.

